## Abstract

**Background:**

Muscle satellite cells (SCs) are crucial for muscle regeneration following muscle trauma. Acute skeletal muscle damage results in inflammation and the production of reactive oxygen species (ROS) which may be implicated in SCs activation. Protection of these cells from oxidative damage is essential to ensure sufficient muscle regeneration. The aim of this study is to determine whether SCs activity under conditions of aseptic skeletal muscle trauma induced by exercise is redox-dependent.

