**Discussion:**

This study is designed to investigate the impact of redox status on SCs mobilization and thus skeletal muscle potential for regeneration under conditions of aseptic inflammation induced by exercise. Findings of this trial should provide insight into (1) molecular pathways involved in SCs recruitment and muscle healing under conditions of aseptic skeletal muscle trauma present in numerous catabolic conditions and (2) whether skeletal muscle’s potential for regeneration depends on its basal SCs content.

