Only two studies have examined the effectiveness of antioxidant supplementation on skeletal muscle healing and the inflammatory response in primary cultured cells and rat gastrocnemius muscle demonstrating that polyphenol administration enhances SCs activation and evokes an earlier appearance of M2 macrophages promoting an anti-inflammatory phenotype [19, 20]. However, no studies have investigated, so far, the effect of redox status perturbations on SCs responses and myogenic potential following aseptic trauma in human skeletal muscle. A powerful antioxidant that has been in clinical and sports performance practice for several decades is *N*-acetylcysteine (NAC). NAC is a thiol donor, non-specific antioxidant with a binary antioxidant role: Firstly, NAC directly scavenges a number of reactive oxygen species (ROS) and secondly, it produces reduced cysteine (Cys) by deacetylation, which supports the biosynthesis of endogenous reduced glutathione (GSH) via the activity of γ-glutamylcysteine synthase [21]. GSH plays a pivotal role in cellular metabolism and especially in terms of stem cells’ oxidative defense, activity, survival and self-renewal under conditions of increased OXS and ROS production [22]. Low to moderate ROS levels control physiological cellular signaling pathways and facilitate muscle growth and development while high ROS levels impair myogenesis and cause cell death through apoptotic and/or necrotic mechanisms (e.g., NF-kB signaling) [23]. We hypothesize that NAC administration following aseptic muscle trauma, characterized by severe inflammation and high levels of ROS, will alleviate the increase in oxidative stress by decreasing ROS activity levels, resulting in an optimal intracellular redox environment, favoring the activity (activation, proliferation, differentiation and fusion) of SCs and thus facilitating muscle’s regenerative process and adaptation following muscle injury. Thus, the objectives of this clinical trial are to examine the effects of redox status perturbation (via NAC administration) on the intracellular pathways responsible for SCs responses following aseptic muscle trauma induced by damaging exercise.

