Following stratification to the HR and LR groups, volunteers of each group will then perform two trials in a randomized order: (1) NAC ingestion and (2) placebo ingestion. NAC or placebo will be consumed before (a 7-day loading phase) and after (immediately post exercise and for eight consecutive days thereafter) an intense eccentric exercise protocol. During both trials, participants will follow the balanced daily dietary protocol of the adaptation period. However, daily dietary intake will be recorded and analyzed during each trial in an attempt to minimize deviations from the prescribed diet. A 4-week washout period will be implemented between trials (dietary intake during this period will also be adjusted according to that applied during the adaptive period). During the entire experimental period, participants will be asked to abstain from any strenuous PA or exercise. Muscle biopsies and blood samples will be collected after overnight fasting before the exercise protocol (pre-exercise sampling) as well as at 2 and 8 days post exercise. Muscle strength and delayed onset of muscle soreness (DOMS) will be evaluated at the same time points. All measurements and collection of biological samples will be performed at the same time of day, in both trials, to prevent circadian rhythm variations. Figure 1 shows the Consolidated Standards of Reporting Trials (CONSORT) diagram of the study and Fig. 2 illustrates the experimental flowchart for the clinical trials.

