All analyses and reporting of the results will comply with the Standard Protocol Items: Recommendations for Interventional Trials (SPIRIT) Statement for reporting randomized clinical trials (RCTs) [57]. Results of participant’s baseline characteristics and outcome variables (primary, secondary and other) will be summarized using descriptive statistics and will be expressed as mean (standard deviation) or median (range) for continuous variables. Data normality will be examined using the Kolmogorov-Smirnov and the Shapiro-Wilk tests. If our data sets follow normal distribution, parametric tests will be applied. Baseline comparisons on the LR and HR groups (anthropometrics, body composition, strength, VO_2max_, dietary profile, PA) will be performed using a one-way ANOVA test. Time- and trial-effect comparisons within and between trial (NAC or placebo) in the LR and HR groups will be analyzed using a two-way repeated-measures ANOVA test with a Bonferroni correction for pairwise comparisons. If the data normality is violated, non-parametric tests will be applied. Baseline comparisons on the LR and HR groups will be performed using a Kruskal-Wallis test. Time-effect comparisons within trial (NAC or placebo) in the LR and HR groups will be analyzed using a Friedman test accompanied by Wilcoxon signed-rank test for pairwise comparisons. Trial-effect comparisons between trials (NAC vs placebo) in the LR and HR groups will be analyzed using a Kruskal-Wallis test accompanied by a Mann-Whitney *U* test for pairwise comparisons. Pearson’s correlation analysis will also be used to examine possible relations among variables. Correlation coefficients of r < 0.2, 0.2 < r < 0.7 and r > 0.7 will be defined as small, moderate and high, respectively. The level of statistical significance will be set at *p* < 0.05. Effect sizes (ES) and confidence intervals (95% CI) will be calculated on results of all dependent variables using the Hedge’s *g* method, corrected for bias. ES will be interpreted as none, small, medium-sized and large for values 0.00–0.19, 0.20–0.49, 0.50–0.79 and ≥ 0.8, respectively. Multiple-imputation analysis will also be utilized to handle missing data during data collection and sensitivity analyses will be executed to evaluate the robustness of the results [58]. Statistical analyses will be performed using the SPSS 20.0 software (IBM Corp., Armonk, NY, USA).

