## Discussion

The present study is designed to assess the impact of redox status on SCs responses and the mechanisms (hormonal regulation, M1 and M2 macrophages, intracellular signaling) associated with their mobilization and function following aseptic skeletal muscle trauma induced by exercise. Nutritional supplementation or medications have been shown to affect SCs biology under traumatic conditions. Hydrolyzed whey protein supplementation and anti-inflammatory medication (ibuprofen) results in increased SCs response and expedites skeletal muscle recovery [25, 48]. Antioxidant supplementation (vitamin C, vitamin E, NAC or combined antioxidants) may attenuate loss of muscle force production and reduce muscle soreness and lipid peroxidation levels but it may also delay recovery suggesting a potential redox-associated mechanism involved in muscle healing [54, 59]. However, this possibility has not been explored in the human skeletal muscle. More specifically, there is no information regarding the redox-dependent mechanism of SCs mobilization and action in human skeletal muscle. It is well established in the literature that thiol oxidation is a major post-translational oxidative modification affecting the cysteine residues in multiple proteins [60]. On the other hand, increased ROS can oxidize GSH leading to irreversible modification [61]. In this sense, low levels of GSH may not only attenuate the antioxidant defense leading to SCs damage but it may also alter cellular redox status drastically. Furthermore, SCs activity is also determined by redox-sensitive cues (cytokines, immune cells, signaling molecules) emerging from the surrounding microenvironment [62]. Supplementation with a powerful GSH precursor, such as NAC, could not only foster GSH levels and thus muscle’s antioxidant potential but also will change myofiber redox balance which is crucial for the redox-dependent regulation of intracellular signaling pathways mediating pro- and anti-inflammatory response to muscle trauma [30]. Our research hypothesis states that NAC-induced change of muscle’s redox status will upregulate SCs availability and mobility under conditions of increased oxidative stress and inflammation in human skeletal muscle. This is of great importance as muscle injury is present in several clinical conditions characterized by increased muscle wasting, atrophy and sepsis that result in physical deterioration and poor quality of life such as in many types of cancer, cachexia, muscular dystrophies, etc. [11, 12]. Consumption of NAC, a potent thiol-based antioxidant, upregulates GSH/GSSG and reduces the respiratory burst and MAPK- and NF-kB-mediated pro-inflammatory cytokine release during inflammation produced by muscle injury [30, 63]. Information derived from this study will elucidate the redox-dependent regulation of intracellular signaling pathways involved in SCs regulation and muscle healing in human skeletal muscle. Therefore, the results of the proposed study should provide information about possible nutritional and/or pharmaceutical interventions to promote SCs function and increase skeletal muscle’s healing potential.

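### The aim is one overall NAC question, but the analysis section compares NAC with placebo within LR and within HR, names no contrast over all men, and does not match the model used for sizing

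*Protocol article*

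**What the plan says.** **The question.** The Abstract (Background) states: "The aim of this study is to determine whether SCs activity under conditions of aseptic skeletal muscle trauma induced by exercise is redox-dependent". The main Background sets the objective: "to examine the effects of redox status perturbation (via NAC administration) on the intracellular pathways responsible for SCs responses". The Discussion gives one directional hypothesis, that "NAC-induced change of muscle’s redox status will upregulate SCs availability and mobility under conditions of increased oxidative stress and inflammation". None of these is limited to LR or HR. The Abstract's Discussion adds a second, separate question: whether muscle's "potential for regeneration depends on its basal SCs content".

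**The design.** Under Study overview and design, "volunteers of each group will then perform two trials in a randomized order: (1) NAC ingestion and (2) placebo ingestion". Every man therefore receives both treatments, with order randomized inside each group.

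**The analysis.** Under Statistical analyses and Power calculation, the parametric plan is: "Time- and trial-effect comparisons within and between trial (NAC or placebo) in the LR and HR groups will be analyzed using a two-way" repeated-measures ANOVA with Bonferroni-corrected pairwise comparisons. The rank-based alternative is framed in the same way: "Trial-effect comparisons between trials (NAC vs placebo) in the LR and HR groups will be analyzed using a Kruskal-Wallis test", followed by pairwise tests.

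**The sizing.** The same section sizes the trial on a within-between interaction in a repeated-measures ANOVA with LR and HR as the two groups. The inputs are effect size 0.55, alpha 0.05, power 0.95, correlation 0.5 and non-sphericity correction 1. The result is 10 per group, raised to at least 12 for 15% dropout.

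**The concern.** The main question concerns all the men studied, but each NAC-placebo comparison in the analysis paragraph is placed in the LR and HR groups. A two-way analysis on trial and time has no place for group. It therefore yields two separate answers per marker, and the text does not say how they combine into an answer to the stated aim. Nor does it name a trial-by-group term, which the second question needs.

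The sizing paragraph does not close the gap. A group-by-repeated-measure interaction asks whether LR and HR differ in their pattern over the repeated measures. That is neither an overall NAC effect nor the trial-by-time analysis described two paragraphs later.

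Two things are at stake: precision on the main question, and the reading of split results. If one group reaches significance and the other does not, it is easy to conclude that NAC works only at one level of satellite-cell content, although that pattern arises readily under a common effect.

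**Working it through.** **1. The plan's own figure.** The default G*Power formula for the within-between interaction is λ = f²·N·m/(1−ρ), df1 = (k−1)(m−1), df2 = (N−k)(m−1). Here f = 0.55 (read as Cohen's f), k = 2 and ρ = 0.5. The number of repeated measurements m is not among the listed inputs, so a range was run.

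| m | Total N for 95% power |
|---|---|
| 2 | 14 |
| 3 | 12 |
| 4 | 10 |
| 6 | 8 |
| 8 | 6 |

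The stated 10 per group (20 in total) is not reproduced by the default. A total of 20 appeared only under non-default readings: leaving out the correlation with m = 3, or halving f to 0.275 with m = 8. The dropout step does reproduce: 10/(1−0.15) = 11.8, so 12.

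**2. By-group against pooled.** Take the within-man NAC-placebo difference, with its SD as the unit, equal groups and the same effect in both. Its variance is 1/12 in one group and 1/24 over both, so each by-group test has half the information. Pooling does not require LR and HR to be alike at baseline, because each man is his own control.

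CI half-width is t(0.975, df)/√n, with df = n−1 for one group and N−2 for both groups with a group term. For n = 12 it is 2.201/√12 = 0.635. For N = 24 it is 2.074/√24 = 0.423. Power is noncentral t, two-sided 0.05, with noncentrality d·√n. The effects d are assumptions.

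| | n = 10 | n = 12 | N = 20 | N = 24 |
|---|---|---|---|---|
| CI half-width (SD) | 0.72 | 0.64 | 0.47 | 0.42 |
| Power, d = 0.5 | 29% | 35% | 56% | 65% |
| Power, d = 0.6 | 40% | 47% | 72% | 80% |
| Power, d = 0.8 | 62% | 71% | 92% | 96% |
| d detectable at 80% power | 1.00 | 0.89 | 0.66 | 0.60 |

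**3. At the protocol's own effect size.** For a within-subject test in one group, λ = f²·n·m/(1−ρ). With m = 2 this is 0.3025·n·2/0.5 = 1.21·n, which corresponds to a paired effect of √1.21 = 1.1. By-group power is then 0.87 (n = 10) or 0.93 (n = 12). With m = 4 it is 0.98 or 0.99. Pooled power is at least 0.996 throughout.

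**4. Split results under a common effect.** The two groups hold different men, so the tests are independent. With power p in each, the chance that exactly one is significant is 2p(1−p). For 12 per group:
- d = 0.5: 2 × 0.353 × 0.647 = 46%
- d = 0.6: 2 × 0.475 × 0.525 = 50%
- d = 0.8: 2 × 0.714 × 0.286 = 41%

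If NAC does nothing, the chance of at least one significant group is 1 − 0.95² = 9.75% per marker.

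**The case against.** The strongest reply is that the article never says the groups are analysed only, or separately. The sizing paragraph puts LR and HR in one model; if that model were fitted with trial as a within-subject factor, an overall NAC effect would be one of its terms. This stands as a limit. A reader might infer that an overall estimate has been ruled out, and the text does not go that far. What it does show is that the two paragraphs describe different models and that neither names an overall NAC contrast. This is more than detail left to a fuller document, because the article fixes the factors and the groups for each comparison.

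The LR/HR split is also deliberate and serves the second stated question, so by-group estimates are legitimate. That stands too, and the remedy keeps them.

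A reader might further infer that a real NAC effect will usually be missed in each group. That fails at an assumed effect of 0.8, where 12 men give 71% power, and at the protocol's own 0.55. Nor is half the data thrown away, since both groups are analysed; the halving applies to each test.

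Finally, one pooled test per marker still leaves about 20 primary markers measured at several times. This is true: the change gives one answer per marker, not one for the trial.

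**Conclusion.** The point holds in this form: the aim, objective and hypothesis are overall; the analysis section, on its natural reading, tests NAC within LR and within HR with no group factor and no stated contrast over all men; and the sample size is tied to a different model.

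Against a pooled analysis, each by-group interval is about 1.5 times as wide (0.64/0.42), and at assumed paired effects of 0.5 to 0.8 power is lower by 25 to 33 percentage points with 12 per group. At the protocol's planning effect the loss is small. Split significance is likely (41–50%) across the assumed effects of 0.5 to 0.8.

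These figures assume equal groups of 12 and a common effect. Twelve is the stated minimum, so larger groups would raise power in both approaches. The mismatch between question, analysis and sizing does not depend on any effect size. It deserves correction before analysis, but it does not invalidate the design.

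**What to change.** In the analysis paragraph, specify one model per marker over all randomized men, with trial, time, LR/HR group and their interactions. Then set the order:

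1. The overall NAC-placebo contrast, giving LR and HR equal weight, is the primary NAC test. State how it is formed over the sampling times.
2. The trial-by-group term (and trial by group by time) addresses dependence on basal satellite-cell content.
3. LR and HR estimates with confidence intervals are reported beside the overall result.

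Frame the rank-based alternative in the same order. Restate the power calculation for this model, including the number of repeated measurements and which term is being powered.

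The cost is wording and one recalculation; the change itself needs no extra men, biopsies or assays. One downside: if LR and HR respond in opposite directions, the overall estimate is an average of the two. The interaction test and the by-group estimates would show this, though the interaction test will be less precise than the overall contrast.

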## Methods/design

### Study overview and design

The methods and ethics of the present study have been approved by the Institutional Review Board of the University of Thessaly (ref. number 1387) and procedures are in accordance with the Declaration of Helsinki, as revised in 2013. The SpEED study incorporates a randomized, two-trial (NAC vs placebo), cross-over, double-blind, repeated-measures design. Participants who will fulfill the inclusion criteria will have their body mass, height, resting metabolic rate (RMR), body composition, muscle strength, soreness and maximal oxygen consumption (VO_2max_) measured. Since protein and antioxidant consumption as well as systematic physical activity (PA) and/or exercise may affect SCs responses and/or redox status, participants’ daily nutrient intake (via a 7-day diet recall with emphasis on protein and antioxidant intake) and PA levels (via accelerometry instrumentation) will be monitored for a week before the inception of the study [24–26]. Then, a 2-week adaptation period (only before the first trial) will be applied to adjust (through a balanced diet, using RMR values and daily energy expenditure measurements) protein and antioxidant intake at the levels required by current Recommended Dietary Allowances (RDAs) (0.8–1 g of protein/kg/day; 900 mg/day of vitamin A; 90 mg/day of vitamin C; 600 IU/day of vitamin D; 15 mg/day of vitamin E; 11 mg/day of zinc; 400 mg/day of magnesium and 55 mg/day of selenium) [27, 28]. This dietary protocol will be designed and implemented by a registered dietician. During the same time-frame, familiarization with experimental procedures will be provided.

Evidence exists that skeletal muscle growth and myogenic potential is directly related to its basal SCs content [24, 29]. As such, volunteers will provide a resting (they will abstain from any exercise or intense PA for at least 5 days prior to sampling) muscle biopsy sample (baseline sampling) from their vastus lateralis muscle (of their dominant limb) and based on its SCs content will be stratified to either high (HR) or low (LR) respondents. Participants will be stratified as HR or LR using a K-means cluster analysis. Blood sampling and performance measurements will also be performed at baseline.

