### Exercise protocol

Participants will perform a protocol consisting of 300 eccentric unilateral maximal contractions (20 sets, 15 repetitions/set, 30-s rest between sets) of the quadriceps muscles on an isokinetic dynamometer (Cybex 770, USA) at a speed of 30°/s. A different limb will be used in each trial. Before the protocol a standard warm up will precede involving 8-min cycling on a cycle ergometer (Monark 834, 154 ERGOMED C, Sundbyberg, Sweden) at a speed of 70 rpm/min and at 50 W, followed by 5-min stretching exercises. KE will be isolated using straps in the shoulders, hips and thigh. This protocol has been described in the literature to effectively induce a significant level of skeletal muscle damage and myofibrillar disruption as documented with electron microscopy and immunohistochemistry [30, 31].

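### The non-parametric fallback compares NAC with placebo by independent-sample tests although every participant takes both, so the test ignores the pairing and is strongly conservative

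*Protocol article*

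**What the plan says.** Under Study overview and design, the article states: "The SpEED study incorporates a randomized, two-trial (NAC vs placebo), cross-over, double-blind, repeated-measures design". It adds that "volunteers of each group will then perform two trials in a randomized order: (1) NAC ingestion and (2) placebo ingestion". Each participant therefore contributes a NAC value and a placebo value for every marker and time point. Under Exercise protocol it says: "A different limb will be used in each trial".

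Under Statistical analyses and Power calculation there are two branches:

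- **Normal data.** Time and trial effects "will be analyzed using a two-way repeated-measures ANOVA test with a Bonferroni correction for pairwise comparisons".
- **Otherwise.** "If the data normality is violated, non-parametric tests will be applied". Time effects within a trial "will be analyzed using a Friedman test accompanied by Wilcoxon signed-rank test for pairwise comparisons". For the treatment effect: "Trial-effect comparisons between trials (NAC vs placebo) in the LR and HR groups will be analyzed using a Kruskal-Wallis test accompanied by a Mann-Whitney".

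"The level of statistical significance will be set at" p < 0.05; sidedness is not stated. No other section offers a paired non-parametric comparison of NAC with placebo.

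**The concern.** Kruskal-Wallis and Mann-Whitney judge a difference against the spread expected when the two sets of values come from different people. Here they come from the same people. Within-person correlation makes the true spread of the NAC-placebo difference smaller than these tests assume, so the null variance is too large and the test rejects too rarely.

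The plan handles the same feature correctly in two neighbouring places: the time comparisons in the fallback branch, and the whole parametric branch. Only the non-parametric treatment contrast, which is the question the trial asks, drops the pairing. The primary outcomes include cell counts per fibre and mRNA fold changes. Such markers are plausibly skewed, so the branch may well be used. For any marker sent there, a real NAC effect is more likely to be missed than the design requires.

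**Working it through.** **1. Inputs from the article.** Two-sequence crossover. Repeated-measures correlation 0.5, significance level 0.05, a minimum of 10 per group, and 15% dropout. The dropout step reproduces: 10/(1 − 0.15) = 11.8, rounded up to 12 per group. That power calculation is for an interaction between the low- and high-respondent groups and the repeated measures. It gives no benchmark for NAC versus placebo, and nothing below depends on how the 10 was reached.

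**2. Assumptions.** The article gives no effect size for the NAC-placebo contrast on its primary markers, so shifts of 0.55, 0.8 and 1.1 SD are assumed. The correlation between a participant's NAC and placebo values is not stated either. The value 0.5 is borrowed from the sample-size input, and 0.3 and 0.7 show the range. Tests are two-sided at 0.05 within one respondent group.

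**3. Why the test is conservative.** With n participants, common SD σ and correlation ρ, the variance of the mean NAC-placebo difference is:

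- assumed by an unpaired comparison: 2σ²/n
- actual: 2σ²(1 − ρ)/n

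At ρ = 0.5 the actual variance is half of the assumed one. Rank tests behave in the same way.

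**4. Simulation.** 20,000 runs per setting; bivariate normal pairs; Mann-Whitney with asymptotic p-values (equivalent to a two-group Kruskal-Wallis) against exact Wilcoxon signed-rank on the paired differences. Mann-Whitney is unchanged by a log transform, so the table also describes lognormal markers when the signed-rank test uses log differences.

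| n | ρ | Shift (SD) | Mann-Whitney | Signed-rank |
|---|---|---|---|---|
| 12 | 0.5 | 0 (size) | 0.9% | 4.0% |
| 12 | 0.5 | 0.55 | 18.6% | 36.9% |
| 12 | 0.5 | 0.8 | 44.2% | 66.6% |
| 12 | 0.5 | 1.1 | 77.6% | 91.1% |
| 10 | 0.5 | 0 (size) | 1.2% | 4.8% |
| 10 | 0.5 | 0.8 | 36.1% | 59.7% |
| 12 | 0.3 | 0.8 | 44.7% | 51.8% |
| 12 | 0.7 | 0.55 | 15.8% | 56.6% |
| 12 | 0.7 | 0.8 | 45.3% | 87.3% |

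**5. Loss at n = 12, ρ = 0.5.**

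- Asymptotic Mann-Whitney: 36.9 − 18.6 = 18.3 points, 66.6 − 44.2 = 22.4 points, and 91.1 − 77.6 = 13.5 points. As shares of the paired power these are 50%, 34% and 15%.
- A second simulation, matching exact Mann-Whitney p-values, gave size about 0.7% and power 17/42/75% against 38/68/91%. The losses are 21, 26 and 16 points, or 55%, 38% and 18%.
- Taken together: about 13 to 26 points, or 15% to 55% of the paired test's power.

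**6. Sensitivity.**

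- At ρ = 0.3 the loss is about 5 to 7 points with asymptotic p-values. With exact p-values it is 54 − 43 = 11 points at 0.8 SD. Allowing for simulation error, the range is 5 to 12.
- At ρ = 0.7 and 0.55 SD the loss is 56.6 − 15.8 = 40.8 points, or 72% of the paired power.
- With signed-rank on raw lognormal differences (log-SD 1, n = 12, 0.8 SD), its power is 59% to 60% at ρ = 0.5 instead of about 67%, and 48% at ρ = 0.3. It still exceeds Mann-Whitney in these settings, by less.

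**The case against.** **It is only a fallback, and it errs on the safe side.** Both points stand. The parametric branch keeps the pairing. A test with a true size near 1% does not inflate false claims of a NAC effect.

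**The correlation is borrowed.** This also stands. The 0.5 was entered for another test, and the two trials use opposite limbs and are separated by a 4-week washout. The NAC-placebo correlation could be lower, and at 0.3 the loss is modest. Opposite limbs still belong to the same person, however, so the samples are not independent by design.

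**The named tests might have a legitimate use here.** Naming Kruskal-Wallis with pairwise follow-up may mean that four cells are compared (two respondent groups by two trials). Mann-Whitney is valid for low against high respondents, because those are different people. It would also be valid on within-person period differences compared between the two treatment orders. The sentence describes neither: it names NAC versus placebo between trials as the comparison, and on that contrast the values are paired.

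**Stronger readings that the article does not support.**

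- A reader might infer that most of the power is lost. At a correlation of 0.5 and a 0.8 SD shift, Mann-Whitney keeps 44.2/66.6, about two thirds. At n = 12, a loss clearly above half needs a higher correlation together with a small effect.
- A reader might infer that about half of perfectly normal markers would be sent to this branch, from 1 − 0.95^12 = 46% or 1 − 0.95^16 = 56%. That supposes independent tests in 12 to 16 cells, with any single failure triggering the switch. The article states no such rule.
- A reader might take the missing mention of Bonferroni in this branch as a decision not to correct. A condensed article may simply leave it out.

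**Conclusion.** The point holds for the non-parametric NAC-versus-placebo comparison. The tests are named explicitly, they assume independent samples, and the article's own design makes the samples paired. This is a wrong stated choice, not a detail left to a fuller plan.

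The contradiction with the design needs no assumption. Its size does: the losses above rest on an assumed correlation and on assumed shifts, and they would be smaller or larger in line with the true NAC-placebo correlation. The practical consequence is a raised risk of reporting no NAC effect for markers that reach this branch. Whether a false negative becomes the likely outcome depends on the true effect: at 1.1 SD and correlation 0.5, even the unpaired test has about 75% to 78% power. The parametric analysis is not affected.

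**What to change.** For the non-parametric NAC-versus-placebo comparison, replace Kruskal-Wallis and Mann-Whitney by:

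- the Wilcoxon signed-rank test on within-participant NAC-minus-placebo differences at each time point;
- for the trial-by-time question, the same test on the NAC-minus-placebo difference in change from pre-exercise;
- log-scale differences for positive, skewed markers;
- the same Bonferroni rule as in the parametric branch.

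If period effects are to be handled, a rank test on within-person period differences between the two treatment orders is a valid alternative, provided it is described as such. Kruskal-Wallis or Mann-Whitney can stay for comparisons of low with high respondents.

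The cost is a change of wording in the analysis section. No additional participants, samples or visits are needed, and the article reports that the trial has not yet commenced, so the change can be made before any outcome data are seen.
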